## Discussion

The result of this trial is expected to provide high-quality clinical evidence that WAA is effective for young females with PD. Acupuncture has been used worldwide for various types of pain [20, 21], and the evidence from clinical studies also suggested that WAA has confirmed analgesic efficacy for many kinds of pain, like post-TACE pain or some cancer pain [15, 21–23]. Nowadays, the incidence of PD is increasing, especially among young females. At present, there are few attentions paid to the application of WAA for PD. Therefore, a trial about this direction deserves our devotion.

Based on TCM acupuncture theory, filiform needle therapy on the acupionts always needs participants to get the sensation of obtaining qi, which is usually experienced as sourness, numberness, distention and pain. Only the acupuncture trial design with request of obtaining qi can reflect the correct and obvious therapeutic effect of acupuncture [24]. Nevertheless, patients who experienced acupuncture treatment will perceive the difference between non-penetrating sham acupuncture and real acupuncture easily. For this reason, it is hard for common filiform needle in acupuncture intervention designed as a blind trial. However, Wrist-Ankle Acupuncture doesn’t require any needling sensation. In the trial, the subjects were asked to wear an eye mask, so it is hard for them to distinguish the certain intervention in the following treatment. For this reason, we believe that non- penetrating sham acupuncture can serve as an effective placebo intervention in this trial. Meanwhile, participants’ feeling of acupuncture questionnaire would arrange in the end of treatment in order to exclude breaking blind subjects. Therefore, a randomized controlled single-blind trial with a non- penetrating sham wrist-ankle acupuncture group was designed, and it will be able to evaluate the immediate analgesia effect of WAA in PD of young females and provide useful advice of evidence-based medicine for further treatment.

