### Data collection

Two identical scale questionnaires should be completed before and after the treatment for assessing the pain-based symptoms of PD in the current menstrual cycle. Participants will complete the first questionnaire 10 min before the treatment, while the second one will be collected immediately after the treatment. The researchers will be present when the questionnaires are completed to ensure the reliability and validity.

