#### Sham acupuncture group

Sham acupuncture was administered on point 1 at both ankles on the first day when the pain occurs during the period. Retain the needle for 30 min. The subjects were asked to wear an eye mask. The target site was also disinfected with an iodophordis infectant (Shanghai Likang Disinfectant Hi-tech Co. Ltd.). The tip and most body of the disposable sterile acupuncture needle will be cut off and blunted (0.25 mm in diameter and 25 mm in length, Suzhou Medical Appliance Factory, Jiangsu Province, China) (Fig. 3). This sham needle has been successfully used in the previous trail design [19]. Only 2-3 mm of the needle body in length was remained. The processed needles were also held with three right-hand fingers (thumb, index finger, and middle finger). The skin near the target site was gently pressed with the left thumb to make it slightly taut. The needle tip was swiftly punctured the skin at the target point at an angle of 30° (The tip actually was not inserted into the skin). Then, the needles remained in the point of skin horizontally for 30 min. The handle was also fixed to the skin with an adhesive tape. For a successful sham treatment, the patient will also only feel a little negligible stabbing pain when the tip of the needle pierces the skin, and no other needling sensation.

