#### Secondary outcomes

The COX menstrual symptom scale (CMSS) will be rated as the main secondary outcomes. The CMSS consists of 18 items and each item has 5 grades according to symptom severity, including the evaluation on general frequency of menstrual symptoms and average severity. 0 point for absence of discomfort; 1 point for mild discomfort; 2 points for moderate discomfort; 3 points for severe discomfort; and 4 points for extremely severe.

Expectation and treatment credibility scale (ETCS), safety assessment, participants’ feeling of acupuncture questionnaire will also be included.

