#### Sample size calculation

The sample size was determined according to the results of our previous pilot study, a two-arm design with WAA group and sham acupuncture group (the response rate was approximately 80% and 40%, respectively, showed by the pilot study). On the basis of the calculation performed by PASS11 with a two-sided significance level of 0.05 and power of 0.80, a total sample size of 52 would be required, with 26 for each group. Considering a maximum dropout tolerance of 15%, 30 initial participants in each group are required for this trial.

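### The stated exclusion of participants who broke the blind, judged after treatment, can bias the randomised comparison by an amount that the protocol does not allow anyone to estimate

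*Protocol article*

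**What the plan says.** The exclusion is in the Discussion of the protocol article, where the sham needle is defended as a credible placebo: the "feeling of acupuncture questionnaire would arrange in the end of treatment in order to exclude breaking blind subjects". Under Secondary outcomes the same instrument is only listed: the participants' "feeling of acupuncture questionnaire will also be included".

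Three other statements bear on it.

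- **Timing.** Under Data collection, the first outcome form is completed before treatment and "the second one will be collected immediately after the treatment". The outcome and the feeling questionnaire therefore fall at about the same time.
- **Cues to allocation.** For the sham, "the patient will also only feel a little negligible stabbing pain when the tip of the needle pierces the skin, and no other needling sensation", and the WAA section expects a similarly slight sensation. Both arms wear an eye mask, "so it is hard for them to distinguish the certain intervention in the following treatment".
- **Numbers.** The sample size section takes pilot results ("the response rate was approximately 80% and 40%, respectively, showed by the pilot study") with a "two-sided significance level of 0.05 and power of 0.80", concludes that "a total sample size of 52 would be required, with 26 for each group", and enrols 30 per group to allow for 15% dropout.

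The exclusion criteria and the Statistical analysis section neither repeat the exclusion nor override it.

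**The concern.** Randomisation makes the arms comparable at the moment of assignment. Removing people by something observed after treatment keeps that comparability only if the removal is unrelated to outcome within each arm. Two routes could make it related.

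1. **Through the outcome.** A woman answering at the end of treatment knows how much her pain has eased and may use that to judge whether the needle was real. By the protocol's own account sight and sensation give her little else to go on, so relief is a plausible cue.
2. **Through the arm.** Only one needle penetrates the skin. If some women detect this, the two arms lose different kinds of participants. That biases the comparison if the women who detect it also differ in pain response.

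At stake is the primary between-group comparison. The exclusion is a stated procedure with a stated purpose, so it is not a detail merely left to an analysis plan.

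**Working it through.** **1. The plan's own sample size.** Inputs from the sample size section: p1 = 0.80, p2 = 0.40, two-sided alpha 0.05, power 0.80. Exact enumeration at 26 per group gives power 0.799 for Fisher's exact test, so 26 is reproduced. Inflation: 26 × 1.15 = 29.9, i.e. 30 (26/0.85 = 30.6 would give 31). The allowance is thus about 30 − 26 = 4 losses per arm.

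**2. Assumptions for the illustration (none is in the documents).** The questionnaire yields a real/sham belief. Let g1 and g0 be the probabilities that a responder and a non-responder believe the needle was real, the same in both arms. Correct guessers are excluded: WAA participants who say real, sham participants who say sham.

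**3. Response rates among those kept.**

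- WAA: 0.8(1 − g1) / [0.8(1 − g1) + 0.2(1 − g0)]
- Sham: 0.4·g1 / [0.4·g1 + 0.6·g0]

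The odds ratio among those kept is the true odds ratio, (0.8/0.2)/(0.4/0.6) = 6.0, divided by the guess odds ratio [g1/(1 − g1)]/[g0/(1 − g0)].

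Example with 0.7/0.3:

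- WAA: 0.24/(0.24 + 0.14) = 0.24/0.38 = 63%
- Sham: 0.28/(0.28 + 0.18) = 0.28/0.46 = 61%
- Kept: 30 × 0.38 = 11.4 and 30 × 0.46 = 13.8

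| g1/g0 | WAA | Sham | Difference | Kept of 30 (WAA, sham) |
|---|---|---|---|---|
| 0.5/0.5 | 80% | 40% | 0.40 | 15.0, 15.0 |
| 0.6/0.4 | 73% | 50% | 0.23 | 13.2, 14.4 |
| 0.7/0.3 | 63% | 61% | 0.02 | 11.4, 13.8 |
| 0.8/0.2 | 50% | 73% | −0.23 | 9.6, 13.2 |

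With symmetric beliefs (g0 = 1 − g1) the effect vanishes when [g1/(1 − g1)]² = 6, that is at g1 = 0.71. With no true effect (40% in both arms), 0.7/0.3 gives 0.12/0.54 = 22% vs 0.28/0.46 = 61%.

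**4. Milder rules.** If only half of the correct guessers are removed, each exclusion probability is halved. For 0.7/0.3, WAA is 0.52/0.69 = 75% and sham is 0.34/0.73 = 47%, a difference of 0.29. For 0.6/0.4, 0.8/0.2 and 0.9/0.1 the differences are 0.35, 0.23 and 0.16: dilution, with no reversal. If correct guessers are removed from the sham arm only, WAA stays at 80% and sham rises to 50%, 61% and 73% for 0.6/0.4, 0.7/0.3 and 0.8/0.2, giving differences of 0.30, 0.19 and 0.07.

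**5. Same pattern with t-tests.** The planned analysis compares scores, so a simulation was run with 30 per arm, 3000 replicates, a true difference of 1.09 SD and all correct guessers removed. As the log-odds of believing real per SD of relief rise through 0.5, 1 and 1.5, the mean estimate falls to 0.56, 0.07 and −0.29 SD. These slopes are assumptions too.

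**6. Loss of numbers alone.** If exclusion is unrelated to relief, only n changes. Power = Φ{[0.4 − 1.96√(2 × 0.6 × 0.4/n)] / √[(0.16 + 0.24)/n]}. This gives 0.91 at n = 30, 0.83 at 24 (20% excluded), 0.77 at 21 (30%) and 0.62 at 15 (50%).

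**The case against.** The strongest reply is that one loosely worded clause in the Discussion carries too much weight here. It could mean ruling out that the blind was broken, i.e. a blinding check; no operative section repeats it; and it does not say which analysis the exclusion would affect. This deserves some weight, but removal is the plainer reading and nothing elsewhere corrects it. If only a check was meant, the sentence still needs changing.

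The second reply is sound and limits the claim. By name, the instrument asks about the feeling of being punctured. A real/sham belief item and a rule that drops every correct guesser are devices of the illustration. At chance guessing such a rule would remove half of each arm, far above the 15% allowance, so it may well not be the rule intended.

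A reader might go further and infer that apparent unblinding is driven by pain relief, so that the exclusion will erase or reverse the treatment effect. The documents do not support that. The link is plausible but inferred, and no guess rates are given. In the illustration, erasure or reversal needs both a strong link and removal of most correct guessers. Nor does it help to note that most women removed from the WAA arm would have improved: at 80% response that is true of almost any removal.

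A reader might also infer that the sample size makes no room for such exclusions at all. It absorbs about four losses per arm of any kind, and whether exclusions would exceed that is unknown.

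**Conclusion.** The point holds as a defect in what is written. A post-randomisation exclusion, based on a questionnaire answered once treatment and its immediate effect are over, is stated outright and can make the compared groups non-comparable.

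Its size and direction are not known. Under the assumed rule that drops all correct guessers, the protocol's difference of 0.40 stays at 0.40 when belief is unrelated to relief, and moves to 0.23, 0.02 and −0.23 as the link strengthens. With half of them dropped it lies between 0.35 and 0.16 for links from 0.6/0.4 to 0.9/0.1. Where there is no link the cost is power only, and only to the extent that total losses exceed the four or so per arm allowed for. All of these figures rest on assumed beliefs and an assumed exclusion rule; they show what the sentence permits and do not predict the trial's result.

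**What to change.** Replace the sentence in the Discussion and carry the same rule into the Statistical analysis section:

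- all randomised participants are analysed in their assigned group as the primary analysis;
- the end-of-treatment questionnaire is reported by arm as an assessment of blinding and removes nobody from that analysis;
- any analysis without apparently unblinded participants is labelled exploratory.

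With everyone kept, the expected rates remain 80% vs 40% on the protocol's assumptions, and power at 30 per arm is 0.91 (normal approximation) or 0.85 (Fisher's exact test). The cost is a sentence or two of wording and no new data. The article reports that recruitment is still under way, so the change can be made before analysis.

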### Trial status

The trial is currently recruiting patients.

## Abbreviations

CMSS: COX menstrual symptom scale
PD: Primary Dysmenorrhea
SF-MPQ: Simple form of McGill pain questionnaire
TACE: Transcatheter arterial chemoembolization
WAA: Wrist-Ankle Acupuncture
